### Clinicians

Participants include clinicians employed by partner clinics who provide outpatient mental health services to children and adolescents. All clinicians who typically provide care in these partner clinics are eligible to participate regardless of their discipline (e.g., psychology, social work, counseling) or professional level (e.g., licensed practitioners, trainees). Partner clinic administrators facilitate communication between study staff and their clinical staff who are eligible to participate. Study staff explain that participating clinicians will be randomized to either the FIRST condition (and thus receive training immediately) or to the UC condition (where they have an opportunity to receive FIRST training at the end of the study). Interested clinicians are sent an electronic consent form.

### Intervention Condition: FIRST

The FIRST treatment condition includes: 1) use of the FIRST treatment manual, 2) an 18-hour training on the content of FIRST and its use with youths 3) weekly small group consultation with FIRST experts to support ongoing fidelity to the treatment, 4) an online learning platform with FIRST resources and 5) an online measurement feedback system that gives clinicians near-real-time data on youth treatment response. The FIRST manual includes skill units (brief one to three page outlines) in the five principles of change (i.e., Feeling Calm, Increasing Motivation, Repairing Thoughts, Solving Problems, and Trying the Opposite) accompanied by worksheets and handouts for youths and their caregivers, as well as skill units specific to Beginning Treatment (e.g., goal setting, engagement, psychoeducation), Ending Treatment (e.g., relapse prevention, termination), and Continuing Treatment/Boosting Engagement (e.g., motivational interviewing strategies to increase engagement in treatment). The manual also includes session content recommendations, in-session activities, and out-of-session assignments related to each principle. The FIRST protocol is designed to be administered to youths, caregivers, and youth-caregiver combinations. FIRST also includes four flowcharts (based on the primary problem) to guide clinical decision-making. The training is a presentation of the manual content that uses experiential activities (video demonstrations, live modeling, and role play) to support learning, and includes time for questions, answers, and discussion. Weekly small group consultation is provided virtually and in-person. Group consultation involves review of performance feedback data for each youth, discussion of the prior session, and planning and rehearsing for the next steps of treatment. Clinicians also have access to an online learning platform with FIRST resources, including the 18-hour initial training, additional video demonstrations of how to use FIRST principles with youths and caregivers, worksheets and handouts, and a discussion board monitored by the study team. Finally, the online measurement feedback system provides clinicians with information regarding clients’ symptoms and functional problems on a weekly basis (assessed weekly via the Idiographic Functional Top Problems Assessment and the Behavior and Feelings Survey; see “Primary Clinical Outcomes”). These data are used to monitor response to treatment and guide treatment decisions.

### Intervention Fidelity

FIRST clinicians have weekly consultation where treatment sessions are discussed. Clinicians follow the FIRST manual with the support of a FIRST expert. All sessions (FIRST and UC) are recorded, and a subset will be coded for fidelity to the FIRST protocol to determine the extent to which EST content was delivered in each condition. A portion of sessions are coded in near-real-time (within a week) with fidelity results shared with consultants.

### Control Condition: Usual Care

UC is the treatment that is usually provided to youths at the partner clinic. This involves the standard training or on-boarding procedures provided to all partner clinic clinicians, and the routine supervision provided. Information on UC is collected via clinician surveys and via coding of a subset of session recordings. Clinicians in the UC condition are not provided access to the FIRST treatment manual, the FIRST training, consultation, online support, or the online performance feedback system.

### Measures

The following measures are collected during the trial (see Table 1 and Table 2 for the schedule of assessments). Measures from clinicians are collected online using Qualtrics. Clinical measures from youth and caregivers are collected via online surveys or telephone calls in which research team members enter data into Qualtrics. All data is stored on a HIPAA-compliant, encrypted shared drive to ensure confidentiality. This shared drive is only accessible to research staff using confidential usernames and passwords. Caregiver measures are available in English and Spanish. When measures did not have previously validated Spanish translations, we followed the gold-standard procedures for translation for cross-cultural research [31]. Procedures involved (1) one bilingual team member translating the measure from English to Spanish; (2) a second bilingual team member who had not seen the original English measure back-translating from Spanish back to English; and (3) a third bilingual team member highlighting discrepancies between the original English and back-translated English versions, the three team members meeting to discuss discrepancies and reach consensus on the Spanish version, with the third team member serving as a tie-breaker as needed. All team members involved with translation were fluent in English and Spanish, and translation procedures were led by a team member with prior experience with these procedures.

### Primary Clinical Outcomes

#### Achenbach System of Empirically Based Assessment (ASEBA) [30].

Youth emotional and behavioral functioning is assessed by ratings from caregivers on the Child Behavior Checklist (CBCL) and by self-ratings on the Youth Self-Report (YSR). Internalizing, Externalizing, and Total Problems scales provide the primary mental health outcomes assessment. The CBCL and YSR have ample evidence for validity, reliability, and sensitivity to change.

#### Behavior and Feelings Survey (BFS) [32].

Weekly assessment of internalizing, externalizing, and total problems will be assessed by the BFS youth and caregiver forms. In prior studies, both youth and caregiver forms showed factor validity, internal consistency, test-retest reliability, convergent validity in relation to three well-established symptom measures (including the CBCL and the YSR), and sensitivity to change during therapy.

#### Functional Top Problems Assessment (TPA) [33].

The TPA assesses severity ratings for the top three functional problems independently identified by the youth and caregiver as most important to address in treatment. The idiographic TPA evidences excellent reliability, validity, and sensitivity to change during treatment.

### Secondary Outcomes (Including Candidate Mediators)

#### Positive and Negative Affect Schedule-Child/Parent (PANAS-C/P) [34].

The 10-item PANAS-C/P includes scales assessing positive affect (5 items, e.g., joyful, cheerful, happy) and negative affect (5 items, e.g., mad, sad, scared). Items are parallel. The 10 items used for this study were identified through item response theory and were shown to accurately classify diagnostic groups in a clinical sample. These 10 items demonstrated similar validity and reliability to the 27-item version [35].

#### Coping Questionnaire [36].

The Coping Questionnaire (CQ) is a measure of youths’ ability to regulate emotions during personally identified upsetting situations. In prior studies, the measure demonstrated strong internal consistency, convergent and discriminant validity, criterion validity, and sensitivity to change during treatment. Prior work also demonstrates that the CQ mediates reductions in anxiety among youths who received treatment.

#### Modified version of the MINI International Neuropsychiatric Interview for Children and Adolescents (MINI-KID-P) [37].

The MINI-KID-P is a standardized diagnostic interview conducted with caregivers to assess the following diagnoses: Major Depressive Disorder, Bipolar I Disorder, Bipolar II Disorder, Other Specified Bipolar, Panic Disorder, Agoraphobia, Separation Anxiety Disorder, Social Phobia, Specific Phobia, ADHD, Conduct Disorder, Oppositional Defiant Disorder, Adjustment Disorder, Obsessive Compulsive Disorder, Generalized Anxiety Disorder, and Persistent Depressive Disorder. We excluded eating, substance-related, and neurodevelopmental modules from administration, with approval from the measure developer. Assessment of these diagnoses were excluded for one or more of the following reasons: 1) included in study exclusion criteria, 2) have a low base rate in school-age populations, or 3) are assessed through other measures. For developmental and practical reasons, we used only the parent-report component (no youth-report) to form these diagnoses, as they were used for aggregate research purposes but not as individual clinical diagnoses. The interview generates reliable and valid psychiatric diagnoses in a brief administration time.

#### UCLA PTSD Reaction Index (PTSD-RI-5) 38].

Posttraumatic stress (PTS) symptoms are assessed using the PTSD-RI-5 administered to the child and caregiver separately. The PTSD-RI-5 is a semi-structured interview that assesses a child’s trauma history and related PTS symptoms. Results are used to ascertain PTSD diagnostic status, inform whether PTS should be a focus of treatment, and monitor PTS clinical outcomes. The PTSD-RI-5 has been widely used to assess PTS symptoms in children and adolescents. Various studies have shown evidence of internal consistency, test-retest reliability, and validity relative to both the degree of trauma exposure and to PTSD diagnoses on standardized interviews [39–41].

### Youth Participant Characteristics

#### Youth Participant Background Form.

Demographic and other background characteristics of youths and caregivers (e.g., race, ethnicity, gender, socioeconomic status) are collected via the caregiver on the youth participant background form developed for this study.

#### Additional Services.

Additional services will be assessed via a newly developed measure based on existing measures (e.g., Services Assessment for Children and Adolescents [42, 43]). In this measure, caregivers report whether youths received any non-study related therapy services since the last assessment, and if so, who provided the service and the treatment target. Caregivers also report youth psychotropic medication use, including start dates, end dates, and the types of medications.

### Measures of Treatment Process and Fidelity

#### Therapeutic Alliance Scale for Children/Parents (TASC-C/P) [44].

The TASC-C/P assesses the quality of the therapeutic alliance with the clinician, as reported by both youths and caregivers. The 7-item TASC-C (child form) has shown good internal consistency and test-retest reliability in samples of clinic-referred youths. Likewise, the 7-item parent measure, TASC-P has shown good internal consistency and test-retest reliability in samples of parents of clinic-referred youths.

#### Therapy Process Observational Coding System-Alliance Scale (TPOCS-A) [45].

The TPOCS-A is an observational coding system applied to recorded therapy sessions by trained study staff that assesses youth-clinician and caregiver-clinician alliance. Psychometric analyses based on youth and caregiver sessions in community outpatient clinics showed that both youth and parent forms have good inter-rater reliability (with most intraclass correlation coefficients in the .50s and .60s), internal consistency (Cronbach’s α= .95), associations with established youth- and parent-report questionnaire measures of alliance, and predictive validity of treatment outcome.

#### Therapy Integrity in Evidence-Based Interventions (TIEBI) [46].

The TIEBI is an observational coding system applied to recorded therapy sessions that assesses the presence/absence of the EST procedures of FIRST, and the competency with which these procedures are delivered (rated from 0 [not present] to 4 [expert]). Mean inter-coder agreement has been shown to be strong for both clinician adherence to FIRST (ICC [1, 1] = 0.87) and clinician competence in delivering FIRST procedures (ICC [1, 1] = 0.88) [28].

#### Weekly Clinician Report of Sessions.

The weekly clinician report of session survey was developed for the current study to collect information about each session. Clinicians in both conditions report the date of the session, the individuals present at the session, broad problems targeted in the session (e.g., anxiety, misbehavior), their overall impression of the session, and their perceived alliance with the individuals present in the session (e.g., youth, caregiver). Clinicians in the FIRST condition additionally report the FIRST principles used during the session.

#### Therapeutic Alliance Quality Rating (TAQR) [47]

The TAQR assesses the clinician’s report of therapeutic alliance with the caregiver and youth. The TAQR uses a single item to assess each relationship. The single item TAQR is strongly correlated with a 52-item clinician scale used to rate youth and caregiver alliance [48].

#### Engagement of Families in Treatment.

Clinic records will provide detailed data on aspects of the treatment process related to engagement. These will include percent of scheduled sessions attended, attended on time, cancelled, and missed due to no-show; and, whether or not treatment was terminated as planned with clinician agreement.

### Post-Treatment Measures

#### Therapist Satisfaction Inventory (TSI) [49].

The TSI is a 16-item clinician-report measure that assesses clinician satisfaction regarding their treatment experience with each youth. Psychometric analyses with 145 youths treated in community clinics by 77 clinicians revealed two psychometrically sound subscales indexing clinicians’ perceptions of treatment effectiveness (α = .82) and responsiveness (α = .81), with clinicians indicating that an EST was perceived as more effective and responsive than UC.

#### Parent and Child Satisfaction Scales (PCSS) [50].

The PCSS is a parallel caregiver- and youth-report measure of treatment satisfaction. Both versions of this measure have previously shown good to excellent internal consistency and test-retest reliability.

#### Perceptions of Supervisory Support Scale (PSSS) [51].

The PSSS is used to assess clinicians’ perceived support in consultation/supervision over the course of treatment with each participant. It is comprised of three subscales including emotional support, support for client goal achievement, and professional development support. It has shown good content validity and reliability.

### Candidate Predictors of Implementation

#### Clinician Participant Background Form.

Background characteristics of the clinicians (e.g., professional discipline, licensure status, therapeutic orientation) are collected via the clinician background form developed for this study.

#### Knowledge of Evidence Based Services Questionnaire-Short Form (KEBSQ-SF) [52].

The KEBSQ-SF is a 17-item self-report measure collected from clinicians to assess their knowledge of practice elements in empirically supported treatments. The measure generates two separate scores: correct endorsements of elements of ESTs and correct rejections of elements without empirical support. The short form has been found to correlate highly with and perform similarly to the well-validated full form of 40 items [53] and demonstrated adequate internal consistency [52].

#### Evidence-Based Practice Attitudes Scale (EBPAS-15) [54].

Clinicians’ attitudes towards ESTs are assessed using the EBPAS, which yields four subscales: appeal (ESTs are intuitively appealing), requirements (would use EST if required), openness (general openness to innovation), and divergence (perceived divergence between EST and current practices). In a large national sample of clinicians, internal consistency was good for the full measure and for the four subscales [53]. Higher scores on the EBPAS openness subscale show convergent validity with clinician-reported cognitive-behavioral therapy use, whereas higher scores on the EBPAS divergence subscale correlate with clinician-reported use of treatment strategies lacking empirical support [55].

#### Evidence-Based Treatment Intentions (EBTI) [56].

The EBTI measures clinicians’ intentions to adopt ESTs clinically. Internal consistency for the scale was good in two studies with community clinicians [57], and the EBTI has demonstrated convergent validity with a measure assessing EST adoption [56].

#### Texas Christian University Organizational Readiness for Change Scale (TCU-ORC) [58].

The TCU-ORC assesses clinicians’ perceptions of the organizational climate of their clinic. Four scale scores will be derived from clinician ratings on this measure: stress (e.g., perceived strain, stress, and role overload); autonomy (e.g., clinician latitude in working with clients); cohesion (e.g., workplace trust and cooperation); and communication (e.g., receptivity to suggestions from staff and utility of information networks). Sound psychometrics for the measure and for these four subscale scores have been reported.

### Sample Size and Power

The target sample size is *N=212* youths. We used Optimal Design [59] to determine power for the main treatment effects, specifically comparing the rate of change for FIRST vs. UC. Assuming at least 24 providers, an ICC of 0.02 (based on prior RCETs), 5 of 6 repeated measures (quarterly schedule, anticipating some missing data), and standard thresholds for significance (α = 0.05), we determined that a minimum sample of *N*= 180 youth participants was required to achieve adequate power (1-β = 0.80) to detect an effect size of 0.50 (based on prior RCETs [15, 16] and a meta-analysis of youth ESTs [1]). Further, we anticipate an attrition/data loss rate of 15% will occur between allocation and analyses. Thus, a target sample size of *N*= 212 youths will ensure adequate power for the primary analyses (Aim 1).

Monte Carlo simulations were conducted in R using the simsem package [60] to estimate power for the Aim 2 mediation analyses. These simulations revealed that 180 participants will provide sufficient power to detect whether FIRST can produce a 0.36-*SD* change in the slope of the CBCL/YSR symptom improvement through the indirect effect of change in negative affect regulation.

Analyses of variables that may be associated with EST implementation (Aim 3) are considered exploratory and therefore were not designed to be adequately powered. Further, available power will vary across models. Nonetheless, power for these models was simulated using the simr package in R [61] which found a sample size of 180 to be adequate to detect a standardized regression coefficient as low as 0.25 for clinician-level predictors/moderators of outcomes within the FIRST condition (anticipating ~ 90 youths across 12–20 FIRST clinicians).

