Latent growth curve (LGC) mediation models will be estimated to test measures of regulation of negative emotions as a candidate mechanism of change. Mediation will be specified using the randomly assigned intervention condition (FIRST vs. UC) as an observed variable, and latent intercepts (baseline levels) and slopes (linear change) in primary and secondary outcomes based on multiple occasions of measurement (e.g., weekly, 0–3-6–9-12–18 months). The LGC models will allow for assessment of whether changes in negative affect (e.g., reduction in negative emotions, increases in coping) that occur early on (e.g., weekly during treatment, or 0–3-6 months) account for symptom change that occur in the long-term (e.g., CBCL/YSR outcome trajectories through 18 months). In this way, these models will achieve the requisite temporal sequence to establish that a variable actually functions as a mechanism of change for mediation.

### Aim 3

Aim 3 analyses will be conducted in an exploratory manner. Data collected from clinicians at baseline in both conditions will be examined in multilevel regression models as level-2 (clinician-level) predictors of level-1 (youth-level) implementation outcomes (e.g., TIEBI-coded adherence and competence). For these models, we will use case-level mean TIEBI scores (i.e., averaging across beginning, middle, and end of treatment scores for each youth) as the outcome variables. As the predictors, we will use scores for measures of clinicians’ baseline knowledge of (KEBSQ), attitudes toward ESTs (EBPAS), motivation to use ESTs (EBTI), and perceptions of organizational climate. Models will be estimated in a hierarchical two-step sequence. In step 1, we will examine these four variables as predictors of implementation outcomes. In step 2, we will test whether these four variables interact with treatment condition; this may clarify whether these evidence-based practice psychological variables predict implementation outcomes differently for those in the FIRST condition as compared to UC.

We used the SPIRIT checklist when writing our report [62].

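### The Aim 3 power sentence credits about 90 FIRST youths with adequate power for a coefficient of 0.25; at two-sided 0.05 only the full sample of 180 supports that figure

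*Protocol article*

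**What the plan says.** The Sample Size and Power section sets its standards in the Aim 1 paragraph: "standard thresholds for significance (α = 0.05") and "adequate power (1-β = 0.80"), with "an ICC of 0.02 (based on prior RCETs"). The minimum analysed sample is 180 youths over both arms, raised to 212 for 15% data loss.

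The Aim 3 paragraph first says that these analyses are exploratory, were not sized for power, and will differ in power from model to model. It then reports a simulation "which found a sample size of 180 to be adequate to detect a standardized regression coefficient as low as 0.25". The scope of that statement is given as "for clinician-level predictors/moderators of outcomes within the FIRST condition", and the sample this implies is put in parentheses: "anticipating ~ 90 youths across 12–20 FIRST clinicians". No ICC, test direction, residual variance or achieved power is given for that simulation.

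Under Planned Analyses, Aim 3, the model is wider than the FIRST arm: "Data collected from clinicians at baseline in both conditions will be examined in multilevel regression models". Each youth contributes one averaged fidelity score as the outcome, and the predictors are clinician-level. A second step adds interactions with condition.

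**The concern.** The sentence names two sample sizes. It calls 180 adequate, but the effect it describes lies within one arm, where its own parenthesis expects about 90 youths. Under 1:1 allocation the other 90 are in usual care and carry no information about a coefficient estimated within FIRST. Because the outcome is one score per youth, repeated sessions add no observations. Because the predictor varies only between clinicians, the effective sample is smaller still.

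What is at stake is interpretation. A reader who takes 0.25 as the detectable coefficient within FIRST may treat a null clinician-level result as evidence against effects of that size, which the arm is not large enough to provide.

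**Working it through.** **Inputs.** Coefficient β = 0.25; about 90 youths and 12 to 20 clinicians in FIRST; 180 analysed youths in total (212 × 0.85 = 180.2); α = 0.05; adequate power 0.80; ICC 0.02. All are from Sample Size and Power. The α, the 0.80 and the ICC are stated for Aim 1 and carried to Aim 3 as an assumption. A two-sided test is also assumed. For both arms together, 24 clinicians is the Aim 1 minimum, and 40 assumes that usual care matches the upper FIRST figure of 20.

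**Formula.** Non-central t with

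NCP = β × √(n / [(1 − β²) × DEFF]), DEFF = 1 + (m − 1) × ICC, m = youths per clinician.

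Degrees of freedom are n − 2 without clustering, and clinicians − 2 for a clinician-level predictor.

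**Step 1: the plan's figure as worded (about 90 youths in FIRST).**
- No clustering: NCP = 0.25 × √(90 / 0.9375) = 2.449, df 88, power 0.68.
- ICC 0.02, 12 clinicians: m = 7.5, DEFF = 1.13, NCP = 2.449 / √1.13 = 2.304, df 10, power 0.55.
- ICC 0.02, 20 clinicians: m = 4.5, DEFF = 1.07, NCP = 2.449 / √1.07 = 2.368, df 18, power 0.61.

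The stated adequacy is not reproduced.

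**Step 2: the same coefficient with all 180 youths.**
- No clustering: NCP = 0.25 × √(180 / 0.9375) = 3.464, df 178, power 0.93.
- ICC 0.02, 24 clinicians: DEFF = 1.13, NCP = 3.259, df 22, power 0.88.
- ICC 0.02, 40 clinicians: DEFF = 1.07, NCP = 3.349, df 38, power 0.90.

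Here the stated adequacy is reproduced.

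**Step 3: what 90 youths can detect with power 0.80.** Solving the same formula for β:

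| Setting | Smallest coefficient |
|---|---|
| No clustering, df 88 | 0.29 |
| ICC 0.02, 20 clinicians | 0.31 |
| ICC 0.02, 12 clinicians | 0.33 |

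Conversely, β = 0.25 without clustering needs about 120 youths within FIRST.

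**Step 4: sensitivity.**
- A Monte Carlo check (8,000 runs per setting, clinician predictor values redrawn each time, t test) gave lower values at ICC 0.02: 0.495 to 0.564 for 90 youths under 12 to 20 clinicians, and 0.827 to 0.876 for 180 youths under 24 to 40. The contrast is unchanged.
- At an assumed ICC of 0.10, the formula gives 0.41 to 0.51 for 90 youths. For 180 youths it gives 0.73 with 24 clinicians and 0.83 with 40, so even the full-sample reading depends on the ICC.
- One-sided 0.05 with 90 youths and no clustering gives 0.78. Four uncorrelated predictors of 0.25 each give 0.77. All 106 randomised FIRST youths with no data loss, two-sided, give 0.75.
- With 90 youths, no clustering and youth-level degrees of freedom, 0.80 is reached only if the whole model explains about 30% of the variance.

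**The case against.** The strongest reply is that the article has already warned the reader: Aim 3 is labelled exploratory, and formal power is disclaimed in the same paragraph. The simulation inputs are not shown and may sit in a fuller document, adequate power is given a number only for Aim 1, and the grammatical subject of the sentence is the sample of 180, for which the figure works. On that reading the fault is a misplaced qualifier and not a failed calculation.

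Much of this stands. It limits the weight of the point, and the article does not show that the simulation itself was done wrongly. It does not rescue the sentence, which names the FIRST arm, its youths and its clinicians. That sample falls short even with no clustering at all. Variants that reach 0.80 need inputs the article does not state, such as a high explained variance with zero clustering. Using all 106 youths with a one-sided test and no clustering gives 0.84, but that departs from the 90 the sentence anticipates.

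A reader might also infer stronger things that the document does not support:
- **Too many predictors for 12 to 20 clinicians.** Planned Analyses names four variables and uses clinicians from both conditions. It does not say that every subscale enters, or that all enter at once.
- **The sentence overstates power for condition interactions.** A 0.25 difference in coefficient between arms would have power of only about 0.4 without clustering. But the sentence speaks of effects within FIRST and does not clearly claim that interaction.
- **The detectable coefficient is really 0.4 to 0.5.** That depends on fidelity ICCs of up to 0.3, which appear nowhere in the article.

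**Conclusion.** The point holds as a minor error in a stated figure. As worded, the Aim 3 sentence claims adequate power for 0.25 within FIRST. Recomputed power is about 0.68 at best under a two-sided 0.05 test, a shortfall of about 12 percentage points against 0.80. For a clinician-level predictor at ICC 0.02 it is about 0.55 to 0.61, a shortfall of roughly 19 to 25 points. The figure is consistent with the full 180 youths, which suggests that the total and the single-arm sample were conflated, though the article does not let this be confirmed.

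The conclusion assumes that the α, ICC and power threshold given for Aim 1 carry over to Aim 3. It would be tempting to infer that the trial is undersized. It is not shown to be: the target of 212 rests on the Aim 1 calculation, and Aim 3 played no part in setting it.

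**What to change.** Correct the sentence in one of two ways.

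1. Keep it about FIRST: restate the detectable coefficient for about 90 youths as roughly 0.29 without clustering and 0.31 to 0.33 at ICC 0.02, note that it grows if fidelity clusters more within clinicians, and report the ICC and power from the simulation.
2. Keep the 0.25: attribute it to the both-arm main-effect model with 180 youths, give the ICC assumed, and say that it covers neither effects within FIRST nor interactions with condition.

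If the simulation used inputs that do support 0.25 with 90 youths, reporting them would also settle the point. The cost is a text change only, with no effect on recruitment, design or the planned models. Under the first option the published figure becomes less favourable; under the second its scope becomes narrower.
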